The objective of this study is to investigate the genetic and epigenetic markers associated with osteoporosis and bone mineral density, and their impact on refracture risk among elderly patients. We aim to collect vertebral body blood and peripheral blood samples from 500 patients with OVCF who will undergo detailed clinical assessments, genome-wide genotype and methylation profiling at baseline. Following the surgical intervention, these patients will be followed up for 1 year to monitor refracture events, during which clinical and genome-wide methylation data will be collected again. These valuable data will enable us to identify genetic and epigenetic markers that can predict OVCF and refracture risk in the elderly and develop accurate prediction models.

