### Sample size

The power of EWAS is essential for detecting differentially methylated positions (DMPs) between cases and controls. Similar to GWAS, the power of EWAS depends on four key factors, including study design, sample size, effect size, and burdon of multiple test correction. Previous simulation analysis has shown that a sample of 500 cases and 500 controls would achieve 80% power to detect differential methylation at epigenome-wide significance (*P* < 1E-6) with a methylation odds ratio of 1.28 or mean methylation differences of 5% in case–control designs of EWAS (cite the original pubication) [19]. Therefore, we aim to recruit 500 elderly patients with OVCF who underwent vertebral augmentation surgery, as well as 500 healthy controls matched for age, gender, and race from the CAS cohort who did not develop OVCF or osteoporosis. This sample size will provide adequate statistical power for detecting significant differences in DNA methylation levels between cases and controls and enable us to identify epigenetic markers associated with refracture after vertebral augmentation surgery for OVCF.

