### Biomarker identification and prediction analysis

The GWAS of bone mineral density will be carried out in PLINK using linear regression model, assuming an additive allele effect. Covariates for age, gender, drug usage and the first five principal components to account for residual population structure will be also included in the model. The genomic control inflation factor will be used to adjust the *p*-values. The adjusted *p*-values equal to or smaller than 5E − 8 will be considered as genoome-wide significant. We will conduct a GWAS using case–control design to invesgate the genetic variants associated with osteoporosis.

This study will use whole-genome methylation data from vertebral and peripheral blood samples of 500 osteoporosis patients with recurrent fractures after vertebral augmentation and 1000 natural population controls from the Chinese Academy of Sciences. To identify differentially methylated positions (DMPs) between patients with and with out refracture, we will perform an epigenome-wide association study (EWAS) and meQTL analysis. Patients with refracture who underwent vertebral augmentation will be selected as cases, and an equal number of patients without refracture will be selected as controls based on age range and epidemiological indicators such as BMI, disease, and medication history. We will analyze changes in methylation levels of osteoporosis- and bone mineral density-related sites in elderly patients with refracture within one year after surgery. The R language DMRfinder package will be used for analysis, and functional annotation of the identified DMPs and differentially methylated regions (DMRs) will be performed.

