### Advanced features of this study

To ensure data quality, we have established a special OVCF real-world research database system that supports data operation traceability, automatic logical verification, and other functions based on the ALCOA principle.We have assigned a special person to inspect the organization and implementation of the study, verify the data, and ensure accurate, timely, and complete data collection through quality control and assurance work meetings attended by all implementation units.To control the risk of loss to follow-up, we have implemented a patient data entry method and set up a special person to supervise the data entry. Follow-up personnel (doctors/nurses) will also follow up on patients’ data entry by monthly or regular telephone follow-up.To control patient compliance bias, we have established a unified clinical research platform for observation indicators such as out-of-hospital medication and dietary habits, and jointly set up personalized anti-osteoporosis programs with the department of endocrinology, rehabilitation, and nutrition to increase patient compliance. The study protocol was designed as a real-world study, and the final analysis was divided into groups according to the completion of the protocol to make the results closer to the clinical situation and increase the credibility of the study.We have implemented strict biobank management, ensuring the samples were only used for this study, destroyed after research, and information leakage was strictly controlled.Our study utilizes a multi-omics approach, incorporating whole genome sequencing and genome-wide methylation analysis to explore the interaction between genetics, epigenetics, and the environment in osteoporosis and bone mineral density phenotypes. This provides a more comprehensive understanding of the molecular mechanisms underlying these conditions.We have included a control group of 1000 healthy individuals from the Chinese Academy of Sciences natural population cohort, providing a larger and more diverse sample for comparison and analysis.We are exploring the feasibility of DNA methylation as a tool for evaluating the effect of postoperative intervention for osteoporosis by analyzing changes in the methylation levels of bone mineral density-related sites in elderly patients with refracture after vertebral augmentation for OVCF within one year after surgery.We are improving the risk prediction model for osteoporosis by incorporating multiple factors such as genetic variation and environmental factors, providing a more personalized approach to prevention and treatment.Our study is conducted in multiple medical centers, increasing the diversity of patient populations and enhancing the generalizability of our findings.

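### The refracture EWAS keeps only an equal number of non-refracture patients although, as the cohort is described, all 500 are already profiled; this loses precision without saving assays

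*Protocol article*

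**What the plan says.** All references are to the protocol article.

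- **Cohort.** The Background plans to sample "500 patients with OVCF who will undergo detailed clinical assessments, genome-wide genotype and methylation profiling at baseline". After surgery, "these patients will be followed up for 1 year to monitor refracture events, during which clinical and genome-wide methylation data will be collected again". The Abstract (Methods) likewise describes 500 elderly OVCF patients undergoing surgery, with one-year follow-up.
- **Refracture comparison.** Under Biomarker identification and prediction analysis, refracture patients are the cases and "an equal number of patients without refracture will be selected as controls based on age range and epidemiological indicators", the indicators being BMI, disease and medication history. No refracture EWAS in the whole cohort is described.
- **Sample size.** The section of that name states that "a sample of 500 cases and 500 controls would achieve 80% power to detect differential methylation at epigenome-wide significance", for a methylation odds ratio of 1.28 or a 5% mean difference at P < 1E-6. That calculation concerns OVCF patients against healthy controls, but the section adds that the same size will "enable us to identify epigenetic markers associated with refracture after vertebral augmentation surgery for OVCF".
- **Final analysis.** Under Advanced features of this study, "the final analysis was divided into groups according to the completion of the protocol to make the results closer to the clinical situation".
- **Conflicting descriptions of the 500.** The Biomarker section also describes the 500 as patients who have refractured. The Eligibility criteria require a refracture after the first operation, and the Inclusion criteria for the control group define patients without refracture as a separate group.

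**The concern.** Taking only some of the available controls makes sense when each extra control costs an assay. If all 500 patients are profiled at baseline, that cost has been met before anyone knows who will refracture. Keeping one comparator per refracture then discards information from the comparison that has least to spare, since the number of refractures may be a small fraction of the 500 assumed in the sample-size statement.

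A smaller, separate matter is the grouping by protocol completion. Completion is known only after surgery, and refracture, death or loss to follow-up may influence it. Results read within completion groups are then conditional on something that may follow from the outcome.

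**Working it through.** **Inputs.** 500 profiled patients (Background). Refracture rate 6.2% to 51.8%, the literature range cited in the Background; the article assumes no rate for this cohort, so 20%, 40% and 50% are my assumptions. Alpha 1E-6, sidedness not stated, taken as two-sided. 80% power at 500 v 500 (Sample size). No SD is given.

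**1. The stated 80%.** It comes from a cited simulation and cannot be reproduced independently without an SD. Under a normal approximation, the standardised difference that gives 80% is (4.892 + 0.842) × √(2/500) = 0.363, which for a 5% difference implies an SD of 0.05/0.363 = 0.138. The figure is sensitive to this: at 500 v 500, an SD of 0.10 gives 99.9% power, 0.12 gives 95.5%, 0.15 gives 64.8% and 0.20 gives 17.4%. I carry 0.363 forward as an assumption.

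**2. Variance, all comparators against 1:1.** With n refractures among 500, the unadjusted ratio is (1/n + 1/(500 − n)) / (2/n). It needs no effect size or SD. At n = 100 it is (0.01 + 0.0025)/0.02 = 0.625, a 37.5% cut; √0.625 = 0.79, so the confidence interval is 21% narrower.

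**3. Power.** Φ(0.363/√(1/n₁ + 1/n₂) − 4.892). At 20% refracture:
- 100 v 100: Φ(2.564 − 4.892) = 1.0%
- 100 v 400: Φ(3.243 − 4.892) = 5.0%

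| Refracture rate | Refractures / others | Left out by 1:1 | Variance ratio | Power 1:1 | Power, all |
|---|---|---|---|---|---|
| 6.2% | 31 / 469 | 438 | 0.533 | 0.03% | 0.17% |
| 20% | 100 / 400 | 300 | 0.625 | 1.0% | 5.0% |
| 40% | 200 / 300 | 100 | 0.833 | 10.3% | 17.9% |
| 50% | 250 / 250 | 0 | 1.000 | 20.1% | 20.1% |
| 51.8% | 259 / 241 | rule not feasible | n/a | n/a | 20.0% |

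At 20% refracture, the difference detectable with 80% power falls from 11.2% to 8.8% on the scale where 0.363 corresponds to 5%. For a larger effect (0.7 SD, purely illustrative), power at 20% refracture goes from 52% to 91%.

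**4. Completion groups.** The article gives no completion rates. If 60% of refracture patients and 85% of the others completed, a true 20% risk would appear among completers as 0.2 × 0.60 / (0.2 × 0.60 + 0.8 × 0.85) = 0.12/0.80 = 15%. Rates of 50%/90% give 12%, and 70%/90% give 16%. This concerns the refracture risk only. If completion depends on refracture alone, the methylation distribution within refracture patients and within the others is unchanged, so the methylation odds ratio is unchanged too.

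**The case against.** **Nobody may be dropped.** If the 500 are all refracture patients, as the Biomarker section and the Eligibility criteria suggest, the non-refracture controls are additional patients. The 1:1 rule would then save assays and the numbers left out could not be calculated. This stands as a condition on the whole point: the Background and Abstract support the reading used here, and the article has to settle which is meant.

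**Outcome-based selection is ordinary.** A nested case-control sample matched on age, BMI, disease and medication history is a recognised design. A reader might infer that the equal-number rule biases the refracture comparison; the documents do not support that, and the loss is one of precision. The variance ratios are unadjusted and give matching no credit for controlling confounding, but adjustment for the same factors in the full cohort addresses that too. Nor are the unselected patients removed from the study: the restriction applies to the refracture comparison, not to the osteoporosis, BMD or prediction analyses.

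**The gain is small in absolute power.** This stands. For the planned effect, even all 500 patients give at most about 20%.

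**Completion is undefined.** A reader might infer that the final analysis is restricted to completers, or that the methylation association is biased. The text speaks of dividing into groups, does not define completion and does not name the EWAS. Bias in the association would need completion to depend also on methylation or its correlates, which nothing in the article shows.

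**Conclusion.** The point holds as one of efficiency, conditional on the 500 being operated OVCF patients who are all profiled and followed. On that reading, 1:1 selection costs precision whenever fewer than half refracture, and above half it cannot be carried out. The size of the loss depends on a refracture rate that the article does not fix: close to half the variance at the bottom of its cited range, nothing at 50%. The variance figures rest only on the cohort size and the rate. The power figures rest in addition on the back-solved 0.363 and a two-sided normal approximation. A reader might infer that using all patients would make the refracture comparison adequately powered; the calculation shows it would not.

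The completion grouping is a secondary point about which analysis should be primary. The 15% against 20% is an illustration under assumed rates, not an estimate of bias in this study.

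**What to change.** 1. State whether the 500 are all operated OVCF patients or only those who refracture, and align the Abstract, Background, Eligibility criteria, control-group criteria and Biomarker section accordingly.
2. Run the refracture EWAS on baseline methylation in all operated patients with follow-up. Take refracture status within one year as the outcome and adjust for the planned matching factors (age, BMI, disease, medication history) plus sex and centre. Use time to refracture only if dates are reliably recorded: the follow-up calls are described as monthly or regular, and Table 1 schedules imaging only before surgery.
3. Keep the 1:1 matched set as a sensitivity analysis.
4. Make the analysis of all operated patients primary and use protocol-completion groups for sensitivity analysis only, with completion defined.

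On the cohort reading, this changes analysis wording and needs no new data. The small downside is reliance on covariate adjustment instead of matching. It is a cheap improvement in precision and should not be presented as a remedy for the low power of the refracture comparison.

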**Discussion:**

This study will be the first large-scale population-based study of osteoporosis and bone mineral density phenotypes based on genome-wide data, multi-time point methylation data, and phenotype data. By analyzing methylation changes related to osteoporosis and bone mineral density in OVCF patients, the study will explore the feasibility of DNA methylation in evaluating postoperative osteoporosis intervention effects. The findings may identify new molecular markers for effective anti-osteoporosis treatment and inform individualized prevention and treatment strategies.

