To predict BMD and OVCF risk, we will use multiple linear regression and multiple logistic regression models, respectively. We will include sex and age as predictors along with independent BMD-related genetic variants identified in previous studies and methylation sites identified in this study. Fracture risk score will also be evaluated based on age, gender, bone mineral density (BMD), previous fracture history, family history, and other risk factors. Prediction accuracy will be estimated using the R-squared correlation (R2) for BMD and the area under the curve (AUC) for OVCF risk. Sensitivities and specificities will be calculated using confusion matrices, where the predicted probability greater than a certain threshold (t) will be considered the predicted shape type, and t will be optimized to maximize the sum of sensitivity and specificity.

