### Clinical implications/impact of the study

The systematic analysis of molecular mechanisms underlying osteoporosis and bone mineral density phenotypes is of great importance, and this study aims to explore cross-omics molecular markers that affect these phenotypes based on multi-omics data and the degree of physiological aging. The research objectives of this study include:Conducting genome-wide association analysis and genome-wide epigenetic association analysis of osteoporosis and bone mineral density to identify genetic and epigenetic molecular markers related to these phenotypes and to deeply analyze their molecular mechanisms.Evaluating the feasibility of DNA methylation in assessing the effect of postoperative intervention for osteoporosis by analyzing changes in methylation levels of bone mineral density related sites in elderly patients with refracture after vertebral augmentation for OVCF within one year after surgery.Improving the risk prediction model of osteoporosis by considering multiple factors such as genetic variation and environmental factors, which can provide a scientific basis for the molecular classification and prevention of related diseases and serve as a paradigm for biomedical researchers conducting multi-omics life data research.

The results of this study can provide valuable insights into the molecular mechanisms of osteoporosis and bone mineral density phenotypes, which can facilitate the development of effective interventions and personalized treatments. The findings can also contribute to the establishment of a risk prediction model for osteoporosis that takes into account genetic and environmental factors, which can help identify individuals at high risk for developing osteoporosis and enable targeted preventive measures. Overall, this study has the potential to make significant contributions to the field of osteoporosis research and improve clinical practice in the management of related diseases.

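### One-year methylation change is planned only in patients with refracture and with no comparator, so it cannot be read as an effect of postoperative intervention

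*Protocol article*

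**What the plan says.** All references are to the protocol article.

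- **Analysis set.** Biomarker identification and prediction analysis states: "We will analyze changes in methylation levels of osteoporosis- and bone mineral density-related sites in elderly patients with refracture within one year after surgery". The second objective, under Clinical implications/impact of the study, carries the same restriction: "sites in elderly patients with refracture after vertebral augmentation for OVCF within one year after surgery". Advanced features of this study and the main Discussion repeat it.
- **Purpose.** The second objective is worded as "Evaluating the feasibility of DNA methylation in assessing the effect of postoperative intervention for osteoporosis by analyzing changes in methylation levels". Advanced features gives the same purpose. The main Discussion goes further and concludes that the study shows the promise of methylation as a marker of how well postoperative intervention works.
- **Wider wording.** The abstract's Discussion does not restrict the set to refracture: "By analyzing methylation changes related to osteoporosis and bone mineral density in OVCF patients". The Background says of the 500 OVCF patients that "these patients will be followed up for 1 year to monitor refracture events, during which clinical and genome-wide methylation data will be collected again".
- **Intervention.** Advanced features describes individualised anti-osteoporosis programmes. No untreated or differently treated group is described. The same section mentions grouping the final analysis by protocol completion, but does not connect this with methylation change.

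**The concern.** Evaluating whether a marker reflects an intervention needs something in the analysis that varies with the intervention. The stated analysis has nothing of the kind. It is a before-after look within one group, and membership of that group depends on an outcome that occurs after surgery.

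Several things other than treatment can move methylation over that year: ageing, recovery from the acute fracture and the operation, and the refracture itself. Without a comparator none of these can be separated from treatment. At stake is the second of three research objectives, and a conclusion in the main Discussion that the analysis could not support whatever the data show.

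**Working it through.** **1. Is there a figure in the plan to reproduce?** No. The 80% power under Sample size (500 cases, 500 controls, P < 1E-6) concerns the baseline case-control comparison. Nothing is stated for one-year change.

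**2. Is a comparator named anywhere?** The candidates are:

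| Candidate | What the article says | Serves as comparator for change? |
|---|---|---|
| Matched patients without refracture (analysis section) | Used to find differentially methylated positions | No; not described as a comparison of change, and no treatment contrast |
| All OVCF patients (abstract) | Wider set for the changes | No; conflicts with the four restricted statements and names no contrast |
| Groups by protocol completion (Advanced features) | Applies to the final analysis generally | No; not linked to methylation |
| Healthy population controls | Case-control comparison | No; not mentioned for change |

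**3. How often would a one-group test reject with no intervention effect?** The article gives no drift size, so this is an illustration on assumed values. Let d be the mean change from causes other than treatment, in SDs of the individual change, and n the number of patients with refracture. For a paired test at two-sided 0.05 (normal approximation):

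rejection rate = 1 − Φ(1.96 − d√n) + Φ(−1.96 − d√n)

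For n, the Background cites a literature refracture range of 6.2% to 51.8%: 500 × 0.062 = 31 and 500 × 0.518 = 259. I add 100 as a middle value. I also add 500, because the analysis section describes the 500 as patients with recurrent fractures.

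At d = 0.2:
- n = 31: d√n = 1.11; 1 − Φ(0.85) gives 20%.
- n = 100: d√n = 2.00; 1 − Φ(−0.04) gives 52%.
- n = 259: d√n = 3.22; 1 − Φ(−1.26) gives 90%.
- n = 500: d√n = 4.47; 1 − Φ(−2.51) gives 99%.

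| Assumed drift d | n = 31 | n = 100 | n = 259 |
|---|---|---|---|
| 0 | 5% | 5% | 5% |
| 0.1 | 9% | 17% | 36% |
| 0.2 | 20% | 52% | 90% |
| 0.3 | 39% | 85% | >99% |

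The error grows with the sample, so recruiting more patients does not help.

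**4. What would a refracture versus non-refracture comparison of change detect?** With n per group, 80% power and two-sided 0.05, the detectable difference in SDs of the change is (1.96 + 0.84) × √(2/n). This gives 0.71 at n = 31, 0.40 at n = 100 and 0.26 at n = 241 (500 − 259 = 241 without refracture at the top of the range). Drift common to both groups cancels. The comparison answers a question about refracture, however, and still does not isolate the intervention.

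**The case against.** The strongest defence is that the aim is worded as feasibility, that this is an article with no success criterion, and that a full protocol or analysis plan may hold the change model. The text is also not uniformly restrictive: the abstract speaks of OVCF patients generally, and the sentence before the quoted one sets up matched patients without refracture.

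Part of this stands. With no test or threshold stated, a reader might infer that the objective is bound to receive a positive answer. The documents do not support that. What they support is that the change would be uninterpretable as an intervention effect. The rest does not rescue the plan. The analysis set is stated four times rather than left open, feasibility of measuring an intervention effect still needs a treatment contrast, and the abstract's wording adds a conflict.

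Two further inferences are tempting and should not be made.

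- **That the sites are chosen from the same baseline samples, so that regression to the mean drives the change.** The article gives no source for the sites in this analysis. Its first objective is "to identify genetic and epigenetic molecular markers related to these phenotypes", which suggests the study's own results. But "methylation sites identified in this study" is said of the prediction models, and the Background also cites earlier epigenome-wide studies. Even if the inference were true, the effect is small at well-powered sites. Selection at 80% power inflates the case-control difference by φ(0.84)/0.80 = 0.35 standard errors. Half of that falls on the cases, and only the non-persistent part regresses: (1 − ICC)/2 × 0.35 × √(2/500). This is 0.002 SD of methylation at an assumed ICC (within-person correlation) of 0.8 and 0.008 SD at 0.3. It shifts the paired z by at most 0.11 with 259 patients. It is larger at poorly powered sites, but it remains secondary to the missing comparator.
- **That a known number of re-profiled patients is left out.** Any count depends on taking the Background's description of the 500 over that in Eligibility criteria and the analysis section, which describe patients who have refractured. It also depends on a literature range given without a follow-up time.

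**Conclusion.** The point holds in this form: the stated one-year change analysis is confined to patients with refracture, has no comparator, and cannot serve the second objective or support the main Discussion's conclusion. This should be corrected. It rests on the text alone and does not depend on how many patients refracture.

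The illustrated rejection rates, about 20% at n = 31 to 90% at n = 259, depend on an assumed drift of 0.2 SD and on applying the literature range to 500 patients over one year. They show how far a one-group test could mislead and do not predict what this study will find. The defect lies in the stated analysis, because the Background says of the followed patients that "during which clinical and genome-wide methylation data will be collected again".

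**What to change.** 1. **Analysis set and model.** Use paired samples of the same tissue from all patients re-profiled at one year. Regress the one-year M value on the baseline M value, age, sex, centre and cell composition. State where the osteoporosis- and BMD-related sites come from.
2. **Intervention aim.** Add recorded treatment received as the exposure, defined in advance, with adjustment for baseline confounders. Do not adjust for refracture: it can occur after treatment starts and be affected by it, so conditioning on it may remove part of the effect or add bias. Label the estimate observational and open to confounding by indication.
3. **Refracture question.** Separately, compare one-year change between patients with and without refracture, and do not present it as an intervention effect.
4. **Fallback.** If the individualised programmes leave no usable treatment contrast, limit the second objective and the main Discussion's conclusion to describing change.
5. **Reconcile the text.** Make the abstract, Background, Eligibility criteria and analysis section agree on who the 500 patients are and whose change is analysed. Show the one-year methylation sample, with its tissue, in Table 1, which lists none.

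**Cost.** On the Background's account no new sampling is needed. The observation indicators already include 36 treatment-plan and 139 follow-up items, and Advanced features mentions out-of-hospital medication. Table 1 schedules medication only at the treatment stage, so the follow-up source of the exposure must be confirmed. The price is slightly more analysis work and a more modest conclusion.
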